## Abstract

**Background:**

Chronic heart failure (CHF) is an increasingly important health problem worldwide. Effective self-care can improve the outcomes and quality of life in patients with CHF. Acknowledging the important role of educational interventions for improving self-care, we sought to assess a new educational strategy involving community health volunteers (CHVs) that could reduce the cost and, hypothetically, increase the effectiveness of self-care education in patients with CHF.

**Methods/Design:**

In this ongoing three-arm controlled trial, approved by two human research ethics committees in Australia and Iran, 231 patients with CHF registered at a referral cardiovascular hospital in Iran were randomly allocated into three groups -trained by community health volunteers at patients’ homes, rained by formal health professionals at hospital; and a control group with no formal educational exposure. Data obtained through interviewing participants and using the Persian self-care of CHF index (pSCHFI) before and two months after interventions will be analysed using SAS and SPSS.

**Discussion:**

The results of this study may help health service systems, especially in countries with limited resources, make use of community volunteers to teach patients with CHF to develop self-care behaviors and skills, reducing the cost of care and improving CHF outcomes. Also, this home-based educational strategy using face-to-face training, if successful, may provide psychosocial supports for patients suffering from chronic illnesses.

**Trial registration number:**

ACTRN12614000788673 (Australian New Zealand Clinical Trials Registry)

## Introduction

### Background

Chronic heart failure (CHF) is an increasingly important health problem with a high mortality rate and morbidity worldwide (Go et al.
2013). Patients suffering from CHF often have a low quality of life (Pinto et al.
2011), and the majority of patients die within five years of diagnosis (Norton et al.
2011). For example, approximately 1.1 million hospitalizations for CHF cost $29 billion in 2004 in the United States (Go et al.
2013), increasing to $40 billion in 2010 and similarly in European countries (Braunschweig et al.
2011). Almost 70% of the expenditure is for hospital services (Heidenreich et al.
2011). Effective self-care behaviors can increase quality of life in patients with CHF and reduce hospitalization (Moser et al.
2012).

Self-care in CHF refers to a naturalistic decision-making process including the choice of behaviours and activities that patients use to maintain life, health and well-being. It includes a healthy lifestyle (e.g. daily exercise), adherence to a treatment regimen, symptom monitoring and seeking assistance when symptoms occur or change (Riegel et al.
2009). Evidence has underscored the importance of knowledge and self-care skills in order to accomplish effective self-care in patients with CHF (van der Wal et al.
2006; Siabani et al.
2013). Health literacy accelerates self-care confidence (Dennison et al.
2011), while lack of knowledge and self-care skills is serious obstacles for patients with CHF and their adherence to treatment (Siabani et al.
2013).

During the past decade many studies have tried and assessed innovative technologies and advanced educational methods to enhance knowledge and self-care skills in patients with CHF (Baker et al.
2011; Barnason et al.
2012; Boyde et al.
2013; Boyde et al.
2011). However, these methods often prove to be ineffective. In addition, almost all interventions have been tried in developed countries rather than in populations living in countries with limited resources. Further, the technology used in these strategies (telehealth etc.) is not available in most less-developed countries. Professional-led programs, as most of these are, require resources that developing countries cannot afford (De Geest et al.
2004). Therefore, educational programs using simple language, minimal technology and taught by dedicated non-professionals is theoretically a more feasible option. Community health workers’ help is a common phenomenon, especially in low- or middle- income countries mainly in the primary care setting (Maes
2010; Hadi
2003; Sirilak et al.
2013; Giugliani et al.
2011).

In Iran, in the past three decades, a new integrated health system has been introduced. It aims to address the Iranian population health needs, especially in rural area and underprivileged urban areas (Asaei
2014; Malekafzali
2006). Obtaining benefit from the help of community health volunteers (CHVs) locally called "*Rabetin Behdasht*" is a part of this system. CHVs are mostly females with basic education – high school or beyond – interested in helping the community health services without pay. The most important role of CHVs in Iran has been building a bridge between people who need follow-up (e.g. vaccination) and health delivery systems. Each CHV covers around 50–100 families living in her neighbourhood. The CHVs are trained after joining the health delivery system and asked to attend once a month at their local health centres to be given the cases for follow up. Evidence showed important progress in improving health indicators such as infant mortality rate across the country following their deployment (Asaei
2014).

To date, CHVs have limited their function to family planning programs and primary prevention (Giugliani et al.
2011; Malekafzali
2006). Recognizing the possibility of role of educational interventions improving self-care in Iranian patients, and the limitation of resources available for this purpose we set out to assess an innovative educational strategy involving CHVs that might reduce cost and, hypothetically, increase effectiveness in improving self-care in patients with CHF.

### Aim and objectives

The aim of this study is to assess the effectiveness of a new educational strategy using CHVs (strategy I) in improving self-care in patients with CHF, in comparison with a formal educational strategy (strategy II) and a control group receiving standard care. The study hypothesis is that CHVs are equally or more effective as professional health educators in educating patients with chronic heart failure to improve self-care skills.

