#### Primary objectives

To determine baseline self-care (self-care maintenance, self-care management and self-care confidence) in patients with CHF discharged from Imam Ali hospital (Iran) from August 2010 to June 2012.

To measure the scores relating to self-care (self-care maintenance, self-care management and self-care confidence) in each of the three arms of the study, two months after applying interventions.

To compare self-care maintenance, self-care management and self-care confidence among groups I and, II, I and III, II and III.

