### Sample size

According to the following formula and information received from another study of a similar design (Riegel et al.
2009), it was expected the mean increase in self-care would be about 22 units (d = 22).

Hence to have a power of 90% (σ =40, d = 22, Z α/2 = 1.96, Z β =0.1) minimum 60 participants were needed for each group.

Considering a non-response rate of 15%, the sample size for each group would be 60, and total of 180 participants. However, according expert opinions, all 231 patients who had completed the primary interviews conducted to obtain the baseline data, and agreed with remaining in the study were considered to participate in the RCT, therefore, each group would be included 77 patients (Figure 
1).

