### Statistical methods

SPSS version 21 and SAS will be used to analyse data. Using descriptive analysis for descriptive data, analytic biostatistics analysis (e.g. ANOVA, independent t-test and paired t-test) for assessing differences (between two groups, among three groups and before and after for each group) will be applied. Regression models will be used to explore associations between predicting factors (e.g. age, gender and education) and self-care scales, and also association between the effectiveness of each strategy and personal characteristics will be used. We will present frequencies and examine the expected associations between different variables to obtain answers for our research questions and hypothesis. T-tests will be used for continuous and normally distributed variables (e.g. self-care maintenance in terms of gender), chi-squared for nominal variables and other proportions (e.g. age group, sex), and multivariate generalized linear regression will be used for detecting associations between outcomes (e.g. self-care management) and explanatory variables (e.g. gender, education and disease duration). Non-parametric tests (e.g., Wilcoxon rank test and Median test) will be used when variables are found not to be normally distributed.

A summary of the interventional strategies is presented in the Table 
1.

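### The hypothesis includes equal effectiveness of volunteers and professionals, but the plan names only difference tests and gives no margin or decision rule that could support it

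*Protocol article*

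**What the plan says.** The Aim and objectives section of the Protocol article gives one study hypothesis: "The study hypothesis is that CHVs are equally or more effective as professional health educators in educating patients with chronic heart failure". It concerns Group I (community health volunteers, CHVs) against Group II (professional educators). The Primary objectives include all three pairwise contrasts on three scales: "To compare self-care maintenance, self-care management and self-care confidence among groups I and, II, I and III, II and III".

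The Statistical methods section lists "ANOVA, independent t-test and paired t-test) for assessing differences (between two groups, among three groups and before and after for each group". It adds that the analysts will "examine the expected associations between different variables to obtain answers for our research questions and hypothesis", without saying what result would confirm or refute the hypothesis.

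The Sample size section uses a single effect: "it was expected the mean increase in self-care would be about 22 units (d = 22", with σ = 40 and a two-sided normal quantile of 1.96. Neither section gives a non-inferiority or equivalence margin, a confidence-interval criterion, or a rule for interpreting a non-significant I-versus-II result.

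**The concern.** The hypothesis has two halves. That CHVs are *more* effective can be shown by a significant difference in their favour, which the planned tests can deliver. That they are *equally* effective can be shown only by ruling out a deficit large enough to matter, and that requires a stated size for such a deficit. A difference test has no such quantity. The 22 points in the Sample size section do not supply it either: they are a gain expected from education, not the amount by which volunteers could fall short and still count as equal.

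Under the named tests, then, the only result bearing on *equally* is failure to find a difference. That result becomes more likely as the data become noisier or fewer, so it rewards imprecision. The article's Discussion and Conclusion address the findings to health systems with limited resources. A claim of equality on this footing could hide a sizeable loss of benefit compared with professional education.

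**Working it through.** **Inputs from the article.** σ = 40; d = 22; two-sided 5% level (1.96); stated power 90%; 77 per arm; 15% non-response, so 77 × 0.85 = 65.45, taken as 65 per arm. Each scale runs from 0 to 100.

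**Assumptions not in the article.** A true I−II deficit of 11 points (half of 22), an illustrative margin of 11 points, and alternative SDs of 20 to 30. Normal approximations throughout.

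**1. The plan's own figure.** The text reads "Hence to have a power of 90"% and then "minimum 60 participants were needed for each group". For two means, n = 2[σ(1.96 + 1.2816)/d]² = 2[40 × 3.2416/22]² = 69.5, so 70 per arm, not 60. With 60 per arm the power is about 85%. With the 77 randomised it is 93% (88% with 65). The discrepancy is a side issue. What matters here is that this is a calculation for detecting a difference, and no companion calculation exists for showing that a difference is small.

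**2. Precision of I−II at σ = 40.** SE = σ√(2/n).
- n = 77: SE = 40√(2/77) = 6.45; half-width 1.96 × 6.45 = 12.6 points.
- n = 65: SE = 40√(2/65) = 7.02; half-width 1.96 × 7.02 = 13.8 points.

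These are 57% and 63% of the 22-point expected gain (12.6/22 and 13.8/22).

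**3. Chance that a real deficit is non-significant.** P = Φ(1.96 − δ/SE) − Φ(−1.96 − δ/SE). For δ = 11 at σ = 40:
- n = 77: 11/6.45 = 1.71, P = 60%.
- n = 65: 11/7.02 = 1.57, P = 65%.

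Other deficits at σ = 40, for n = 77 (65): 5 points, 88% (89%); 10 points, 66% (70%); 15 points, 36% (43%); 22 points, 7% (12%).

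**4. Sensitivity to the SD, δ = 11.**

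| SD | Non-significant, n = 77 | Non-significant, n = 65 |
|---|---|---|
| 40 (article) | 60% | 65% |
| 30 (assumed) | 38% | 45% |
| 25 (assumed) | 22% | 29% |
| 20 (assumed) | 7% | 12% |

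**5. What a non-inferiority rule could deliver.** With true difference zero and the lower limit of the two-sided 95% interval compared with −Δ, power = Φ(Δ/SE − 1.96).
- Δ = 11, σ = 40: 40% (n = 77), 35% (n = 65).
- Δ = 11, SD 20: 93% (n = 77), 88% (n = 65).
- Smallest Δ reaching 80% power at σ = 40: (1.96 + 0.8416) × SE = 18.1 points (n = 77), 19.7 points (n = 65). For 90% power with n = 77: 3.2416 × 6.45 = 20.9 points.

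**The case against.** The strongest reply is that the article never says a non-significant result will be taken as equality. That is correct. A reader might infer that failure to reject will be reported as proof of equality, or that the trial is set to conclude that volunteers can replace professionals. Neither statement is in the document. It is silent on interpretation, its test list is introduced as examples, and nothing prevents a confidence interval from being reported. The defect is an undefined decision rule, not a prescribed wrong one.

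Second, non-inferiority may not be the central claim. The Conclusion restates the hypothesis more weakly, as volunteers being able to train patients in self-care and possibly doing so more effectively. The planned comparisons with control and between the two educated groups address that. This narrows the point to the word *equally*. It does not remove it, because the Aim and objectives section still states it as the hypothesis.

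Third, σ = 40 is large for a 0–100 scale, and the 11-point deficit is the reviewer's choice. Both are true, and the table above shows how much depends on them. At an SD of 20 the problem is modest in size, although the missing rule remains.

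A last reply is that such detail belongs in a fuller plan. But the article itself states the hypothesis, the effect size and the tests, and those three do not match. That is a conflict between stated elements rather than an omission.

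**Conclusion.** The point stands, confined to the *equally* half of the hypothesis. The article states that half, but names only difference tests and a difference-based sample size, with no margin or decision rule. No analysis it names can therefore support it. A non-significant I-versus-II test would be weak evidence: at the article's σ = 40 a true 11-point deficit would go undetected 60% of the time with 77 per arm and 65% with 65. At an assumed SD of 20 those figures are 7% and 12%. The mismatch depends on none of these assumptions; only its practical size does. A significant I-versus-II result favouring CHVs would still support *more effective*, and the contrasts of either educated group with control are untouched.

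**What to change.** Settle this before follow-up data are analysed, by one of two routes.

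(a) The simpler route, given that groups are already allocated: drop *equally* from the hypothesis, report the I−II difference with its 95% confidence interval on each of the three scales, and state that a non-significant difference will not be interpreted as equivalence.

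(b) Keep the hypothesis, and conclude that CHVs are equally or more effective only if the lower limit of the two-sided 95% interval for I−II lies above −Δ. Fix and justify Δ in advance, name the scale or scales on which the criterion must hold, and test superiority only after it is met. Δ should not simply be a fraction of 22, because the Sample size section does not say whether that figure is a before–after change or a gain over control. State the power that 77 per arm gives: at σ = 40 only margins of about 18 points or more reach 80%, and such a margin would be most of the 22-point expected gain.

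Both routes use the same data and planned contrasts; only wording and analysis rules change. The cost is that a claim of equal effectiveness is withdrawn under (a) and becomes harder to reach under (b), possibly with low stated power.

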### Intervention

#### Educational approaches

The intervention included two different educational approaches to training self-care information to patients diagnosed with CHF. One group was trained face-to-face at their homes by CHVs and the second group was trained by a skilled nurse and a general practitioner in three small groups at a conference room in the hospital (Imam Ali Hospital).

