#### Preparing educators

Prior to the intervention ten female CHVs, aged from 27 to 53 years were trained in three workshops by a general practitioner. These subjects were selected from among fifty CHVs connected to a health delivery center (Sameno-al-aemaeh) in Kermanshah. The inclusion criteria were; an acceptable level of conversation skills, ability to speak in Persian and Kurdish, having been actively involved during the preceding year in assisting at the health center and having graduated from high school or beyond. Three one-day workshops were held to train and prepare the selected CHVs, the number and duration of workshops being based on a needs-assessment conducted at the introductory session and using the feedback from participants (CHVs) after that session.

The aim of workshops was to teach the CHVs about the content of the educational programs for patients and how to present the information. The materials were obtained from heart failure text books (Bonow et al.
2011) and related sites (Krum et al.
2011) that have been translated into simple Persian language understandable for patients, even those who might be illiterate. The preparation and simplification was conducted under supervision of a cardiologist. The information was provided in a PowerPoint presentation and in a notebook used in workshops. In addition, during workshops, tutors considered the likely questions or challenging issues that might be faced during their home visits. At the end of the workshops, using role play, each of CHVs was assessed to evaluate her ability as an educator. One of CHVs who did not have an acceptable result was removed from the list. Further, CHVs were given a contact number of a trained general practitioner to ask questions during home visits.

For the second group a nurse and general practitioner both experienced and working in cardiovascular disease and cardiovascular rehabilitation were employed. They were asked to study the notebook prepared as above. They were asked to educate participants, using their own knowledge and considering the aims and objectives of education. They were blind to the study purpose.

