#### Payments

The interventions were started in parallel, though educating by CHVs lasted about two weeks because each CHV had to educate approximately seven to eight patients one-by-one and at their homes. The patients in second group –educated at hospital– were offered reimbursement for travel costs but none asked. Fees were paid to educators of this group, namely, the nurse and general practitioner. CHVs making home visits were reimbursed for travel costs. Taxi fares were paid for one of the investigators who monitored the home-based education. Two months later participants in the three groups were interviewed again at home or hospital, according to their preferences.

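### The study hypothesis is about who teaches, but arms I and II also differ in setting, format and hours, so the I versus II contrast supports a comparison of strategies and not of educators

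*Protocol article*

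**What the plan says.** The protocol article puts two differently worded statements next to each other in Aim and objectives. The aim is "to assess the effectiveness of a new educational strategy using CHVs (strategy I) in improving self-care in patients with CHF", compared with a formal strategy (strategy II) and with standard care. The hypothesis that follows is that "CHVs are equally or more effective as professional health educators in educating patients with chronic heart failure to improve self-care skills". The aim compares strategies; the hypothesis compares kinds of educator.

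Primary objectives lists the contrasts: "To compare self-care maintenance, self-care management and self-care confidence among groups I and, II, I and III, II and III".

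The arms are described as follows.

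- Arm I (Educational approaches): "One group was trained face-to-face at their homes by CHVs". Payments adds that "each CHV had to educate approximately seven to eight patients one-by-one and at their homes". Table 1 gives 2 hours.
- Arm II (Educational approaches): "trained by a skilled nurse and a general practitioner in three small groups at a conference room in the hospital". Table 1 gives 4 hours.

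The Conclusion describes what the study was designed to examine as CHVs teaching face-to-face in patients' homes, which names the format and setting together with the educator.

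**The concern.** The hypothesis varies one factor, the educator. The design varies several at once. A result for arm I against arm II could then be credited to, or blamed on, the wrong component.

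If arm I does as well as arm II or better, individual teaching at home could account for some or all of it, and the result would not show that CHVs teach as well as professionals. If arm I does worse, the shorter contact time could be the reason, and the result would not show that CHVs are the poorer teachers.

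This matters because the article expects the findings to inform whether health services with limited resources use volunteers to teach patients. A reader who takes the hypothesis literally would carry an educator effect over to other settings, formats and durations, where this trial has no information.

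**Working it through.** The plan gives no figure that bears on this point, and the Sample size calculation does not enter. The check is whether any planned contrast isolates the educator.

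**Step 1. Features of the two teaching arms**

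| Feature | Arm I | Arm II | Where stated |
|---|---|---|---|
| Educator | CHVs | Nurse and general practitioner | Educational approaches; Table 1 |
| Setting | Patients' homes | Hospital conference room | Educational approaches; Table 1 |
| Format | One-to-one | Three small groups | Educational approaches; Payments; Table 1 |
| Duration | 2 hours | 4 hours | Table 1 |

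As planned, every patient in arm I has the whole left-hand column and every patient in arm II the whole right-hand column. Setting, format and duration do not vary within an arm.

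**Step 2. What each contrast estimates**

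Write E for the effect of having a CHV and not a professional as educator. Write S for the joint effect of the arm I setting, format and hours as against those of arm II, including any interaction with the educator.

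- I minus II has expectation E + S.
- I minus III has expectation equal to the whole effect of the arm I package against no education.
- II minus III has expectation equal to the whole effect of the arm II package against no education.
- (I minus III) minus (II minus III) = I minus II, so the control arm adds no further equation for E.

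There is one equation for two unknowns. Separating E from S would need at least one arm in which the educator changes while the rest stays fixed, such as professionals teaching individuals at home for the same time. No such arm exists.

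**Step 3. Illustration (assumed values on the 0 to 100 scale, not from the article)**

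| E | S | Expected I minus II = E + S |
|---|---|---|
| -10 | +10 | 0 |
| 0 | 0 | 0 |
| -5 | +10 | +5 |
| 0 | +5 | +5 |
| +5 | 0 | +5 |

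A difference of 0 fits CHVs who are equal to professionals and CHVs who are 10 points worse. A difference of +5 fits CHVs who are worse, equal or better. A larger sample narrows the interval around E + S and leaves E undetermined. Regression on patient characteristics does not help either, because the three features coincide with arm.

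**Step 4. Content**

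Preparing educators says of the CHVs' training: "The aim of workshops was to teach the CHVs about the content of the educational programs for patients and how to present the information". Of the arm II educators it says they were to study the same notebook, and then: "They were asked to educate participants, using their own knowledge and considering the aims and objectives of education". The source material was therefore shared, while arm II delivery was less standardised. Steps 1 to 3 do not depend on this.

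**The case against.** The strongest reply is that this is an ordinary pragmatic comparison of two deliverable programmes. The aim, the abstract, Trial design and Table 1 all speak of strategies, and the Conclusion names home and face-to-face delivery with the CHVs. On this view the hypothesis sentence is shorthand. Much of this stands. The I versus II contrast is a valid randomised comparison of the two strategies, and the Conclusion needs no rewording on this account. What does not stand is that the hypothesis can be left alone: it is the sentence against which results will be judged, and it names only the educator.

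Three stronger readings are tempting and are not supported.

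- *That the trial cannot answer its question at all.* It can answer the strategy-level aim and the third primary objective. Only attribution to the educator is out of reach.
- *That the Table 1 entry of near-identical materials is wrong because arm II taught from its own knowledge.* Those educators were also asked to study the notebook used in the CHV workshops. Adding one's own knowledge to shared materials does not contradict a row headed Materials.
- *That arm II was taught in classes of about 26.* This is 77/3 = 25.7, which assumes equal groups and full attendance. The article gives no group sizes, and the argument needs only the contrast between individual and group teaching.

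That arm II relied on one nurse and one general practitioner is a question of generalisability. It is separate from this point.

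**Conclusion.** The concern holds in a limited form. The educator effect named in the hypothesis is not identifiable from any planned contrast, because setting, format and duration change completely with the educator. The size of the resulting bias cannot be stated: it equals S, which the design does not estimate, and the values in the illustration are assumptions. The conclusion rests only on the arm descriptions in Educational approaches, Payments and Table 1. It does not depend on whether delivered content differed.

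The randomisation, sample size and strategy comparison are unaffected. The consequence is confined to what may be concluded: a difference, or a similarity, between arms I and II is evidence about the two packages as delivered.

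**What to change.** In Aim and objectives, reword the hypothesis to match the aim beside it, for example: *individual 2-hour home education by CHVs is equally or more effective in improving self-care than 4-hour small-group hospital education by a nurse and general practitioner.* Add one sentence stating that a difference or similarity between arms I and II will not be attributed to the type of educator alone. It would also help to note that arm II delivery was less standardised, since its educators drew on their own knowledge as well as the notebook.

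The interventions are described as already delivered, so adding an arm that separates the factors is not a practical remedy here. The article reports no results yet, so the wording can still be settled before they appear. No change to arms, data collection, sample size or analysis is needed. The cost is a narrower claim: the trial would no longer speak to whether volunteers teach as well as professionals under the same conditions.
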